#### Candidate gene expression analysis

2.7.4

Targeted gene expression analysis will be performed to examine the functional relevance of the key circadian and sleep-related genes. RNA will be extracted from buffy coat samples using the PAXgene Blood RNA Kit (PreAnalytiX, Switzerland), which preserved the *in vivo* gene expression profile at the time of blood collection.

Quantitative real-time PCR (qRT-PCR) will be performed using a focused panel of candidate genes.

*Core circadian clock genes*: *CLOCK, ARNTL/BMAL1, PER1, PER2, PER3, CRY1, CRY2, NPAS2*

*Clock-regulated genes*: *SIK1, SIK2, GSK3B (Glycogen Synthase Kinase 3 beta)*

*Neurotransmitter-related genes*: *COMT (Catechol-O-Methyltransferase)*

Gene expression levels will be normalized to housekeeping genes (*GAPDH* and *ACTB*) and will be expressed as fold-changes relative to a pooled reference sample.

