#### Sample collection and processing

2.7.1

Venous blood samples (10 mL) are collected from all participants at the baseline visit using EDTA tubes to preserve nucleic acids. The blood samples are processed within 2 h of collection. The samples are centrifuged at 2000×g for 10 min at 4°C to separate the plasma from the cellular components. The buffy coat layer, which contains leukocytes rich in DNA and RNA, will be carefully extracted and aliquoted into cryovials. Plasma will be similarly aliquoted for potential biomarker analysis. All samples are labeled with unique study identification codes and stored at -80°C until analysis.

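### The RNA kit is credited with preserving gene expression as it was at the blood draw, but it is first used on EDTA buffy coat that has already waited up to 2 h, been spun and been frozen

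*Protocol article*

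**What the plan says.** Section 2.7.1 (Sample collection and processing) sets out how the blood is handled. Samples are "collected from all participants at the baseline visit using EDTA tubes to preserve nucleic acids". On timing it says "The blood samples are processed within 2 h of collection". They are then centrifuged at 2000×g for 10 min at 4°C "to separate the plasma from the cellular components", and the buffy coat "will be carefully extracted and aliquoted into cryovials". All samples are "stored at -80°C until analysis".

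Section 2.7.4 (Candidate gene expression analysis) says "RNA will be extracted from buffy coat samples using the PAXgene Blood RNA Kit". It credits that kit with having preserved the in vivo "gene expression profile at the time of blood collection". Expression of 12 candidate genes, eight of them core clock genes, is then normalised to GAPDH and ACTB and expressed as fold-change against a pooled reference.

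Section 2.7.5 interprets expression patterns as the participant's molecular state and plans to relate them to the fNIRS findings. Section 2.8.7 plans a differential expression analysis with correction for multiple testing.

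**The concern.** A kit can act on RNA only from the moment it is applied. If it is first applied to stored buffy coat, it cannot hold expression at the level it had when the blood left the vein. Any change during the wait, the spin or the freezing is already in the sample.

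What is at stake is the meaning of the expression variable. The preservation claim tells analysts and readers that the interval between draw and freezing can be ignored. If it cannot, a measured value combines the participant's biology with whatever handling did. Variation in handling that is unrelated to cohort would add noise. Variation that differed between the cohorts, or over the recruitment period from March 2023 to October 2024, could appear as a difference in expression.

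**Working it through.** **Order of steps, from the text alone**

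| Step | What is described | Section |
|---|---|---|
| 1 | Draw into EDTA tube, the only collection tube named | 2.7.1 |
| 2 | Processing within 2 h; holding temperature not given | 2.7.1 |
| 3 | Spin, 2000×g, 10 min, 4°C | 2.7.1 |
| 4 | Buffy coat aliquoted into cryovials | 2.7.1 |
| 5 | Storage at -80°C | 2.7.1 |
| 6 | RNA kit applied to buffy coat | 2.7.4 |

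The kit enters at step 6. The property claimed for it belongs to step 1. At best the kit recovers the profile as it stood after steps 1 to 5. No outside source is needed to see this.

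**Does anything else in the article supply the missing preservation?**
- Section 2.7.1 says EDTA tubes are used "using EDTA tubes to preserve nucleic acids" (part of the wording quoted above). That is a general remark about the tube. It does not say that expression is held at its level at the draw, and Section 2.7.4 credits the kit, not the tube.
- Normalising to two housekeeping genes corrects for the amount of RNA put in. It does not by itself remove changes during handling that differ from gene to gene.
- The purity and concentration criteria in Section 2.7.2 are for DNA. No RNA criterion is given.

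**Size**

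The plan has no figure to reproduce, and the documents give no drift rate, no handling times and no between-cohort difference. The following only shows what would matter. All inputs except the group sizes are assumptions.

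- Group sizes: 249 and 89 (Section 2.9). These are upper limits, because Section 2.3 provides compensation for participants who complete everything except fNIRS and blood sampling.
- Assumed drift b: 0.1 to 0.5 cycles per hour. Assumed between-person SD: 0.8 cycles. Assumed delay: uniform over 0 to 2 h, with SD 2/√12 = 0.577 h.
- Total SD = √(0.8² + (0.577b)²), which is 0.802, 0.819 and 0.850 at b = 0.1, 0.3 and 0.5.

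*Equal delay in both cohorts.* A test with 80% power when there is no handling noise keeps 79.8%, 78.2% and 75.0% power at the three drift values.

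*Mean delay differing by g hours.* Shift = b × g; d = shift / total SD; rejection from the noncentral t with 336 degrees of freedom and noncentrality d × √(249 × 89 / 338) = 8.10d, two-sided 5%, no multiplicity correction.

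| b (cycles/h) | g = 0.25 h | g = 0.5 h |
|---|---|---|
| 0.1 | d 0.03, 5.7% | d 0.06, 7.9% |
| 0.3 | d 0.09, 11.5% | d 0.18, 31.6% |
| 0.5 | d 0.15, 22.1% | d 0.29, 66.0% |

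With a Bonferroni threshold of 0.05/12 over the 12 genes, the same grid runs from 0.5% to 31%. Two cohorts that are both uniform over 0 to 2 h cannot differ in mean delay, so the second table joins a mean difference to a variance model that does not strictly allow it. That is one more reason to treat it as a scenario and not as an estimate.

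**The case against.** The strongest objection is that no bias is shown. Nothing in the documents says that these genes drift within 2 h, that handling time differed between cohorts, or that it changed over the study. Both cohorts follow one procedure with one 2 h ceiling. A reader might infer from the contradiction that the expression comparison is biased, or take the 66% corner of the table as a false-positive rate. The documents support neither. That corner needs the largest assumed drift together with a between-cohort gap equal to a quarter of the 2 h window, in an uncorrected test. If delays are equal, little power is lost. This objection stands in full.

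Second, the absence of a handling covariate or batch term is detail that a condensed article may leave to a laboratory manual or analysis plan. The article also merely mentions no RNA stabiliser; it does not say that none was used. Both points stand, and neither omission is counted here as an error. What remains is that the article states the handling sequence and also states a property which that sequence does not have. If a stabilising tube was in fact used, Section 2.7.1 is incomplete or wrong instead, and the sections still need reconciling.

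Third, expression is not central to the study. The primary genomic analysis is the polygenic score (Section 2.7.3), clustering uses digital features (Section 2.8.4) and the ISI is the primary severity outcome (Section 2.4.1). This limits the weight of the point without removing it.

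**Conclusion.** The point holds as a contradiction between Sections 2.7.1 and 2.7.4. As written, the assay measures expression in EDTA buffy coat after a handling interval that can vary, and the claim that the profile at the draw was preserved is unsupported. It follows that the molecular-state reading in Section 2.7.5 is too strong.

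This conclusion rests on the order of steps as described and on no assumption about drift. The size and direction of any effect on results cannot be derived from the documents. Delay can enter the expression values; whether it did, and whether it did so differently in the two cohorts, is unknown. The matter is confined to the candidate gene expression component and the analyses that use it.

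**What to change.** 1. Reconcile Sections 2.7.1 and 2.7.4. Either correct the description of the collection tube and RNA source, if a different one was used, or replace the preservation claim with what was done: expression in EDTA buffy coat processed within 2 h of the draw.
2. Unless a different tube or RNA source is documented, limit the interpretation in Section 2.7.5 accordingly, so that expression is read as a post-handling measurement.
3. Where draw and processing times were logged, include the draw-to-freeze interval and extraction batch as covariates in the expression models. An analysis restricted to samples with short intervals is optional support; it would shrink an already unbalanced sample.
4. If times were not logged, say so as a limitation. The genomic limitations in the Discussion do not mention handling.

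Collection is complete, so only wording and analysis can change. The cost is a slightly weaker claim and one or two extra covariates. The documents do not say that per-sample times exist; a 2 h limit can be kept by workflow without recording them, so step 3 is conditional.

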#### Data integration strategy

2.7.5

Genomic and biomarker data is designed for integration with clinical, digital phenotyping, and neuroimaging measures. The analytical framework conceptualized PRS as representing “genetic vulnerability,” gene expression patterns as “molecular state,” and biomarker levels as “physiological output” in the context of environmental and behavioral modulating factors captured through digital phenotyping.

This multi-omics integration approach will enable the investigation of gene-environment interactions, identification of molecular subtypes, and development of personalized risk prediction models. Specific analytical plans will include correlating PRS with digital phenotypes, examining gene expression patterns in relation to fNIRS findings, and testing whether genomic profiles modify the relationship between environmental factors and sleep outcome

### Data analysis plan

2.8

The analytical strategy was designed as a multitiered approach, progressing from traditional statistical methods to advanced computational techniques to fully leverage the rich multimodal dataset. The analysis plan addressed three primary objectives: (1) characterizing the differences between insomnia and control groups, (2) identifying data-driven insomnia subtypes, and (3) developing predictive models for personalized sleep medicine.

#### Preliminary data analysis and quality control

2.8.1

Data preprocessing: All datasets will undergo comprehensive quality-control procedures. Digital phenotyping data will be screened for outliers using interquartile ranges and temporal consistency checks. The clinical assessment data will be examined for completeness and consistency. fNIRS data undergo standard preprocessing, including motion artifact correction and signal quality assessment. Genomic data quality control will follow the established GWAS protocols.

*Missing data strategy*: Clinical and self-report variables will be handled using multiple imputation by chained equations (MICE) under the Missing at Random (MAR) assumption. For digital phenotyping data with systematic missingness (e.g., device non-wear periods), short-term gaps will be interpolated using Kalman smoothing to preserve temporal continuity, whereas longer missing periods will be excluded from time-series analyses. Sensitivity analyses will assess the impact of missing data assumptions on the primary findings.

*Descriptive statistics:* Comprehensive descriptive analyses will characterize both cohorts across all measurement domains. Continuous variables will be summarized using mean, standard deviation, median, and interquartile ranges. Categorical variables will be presented as frequencies and proportions. Data distributions will be assessed using histograms, Q-Q plots, and normality tests to inform subsequent analytical choices.

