### Digital phenotyping

2.5

Digital phenotyping serves as a core methodological component of this study, using a wearable device and smartphone application for continuous monitoring of participants’ behavioral and physiological parameters. A custom-designed smartphone application, named “SOMDAY” (Lumanlab Inc., Seoul, Republic of Korea), is installed on the participants’ personal smartphones. The name combines “SOM” (from ‘somnus,’ the Latin word for sleep) and “DAY,” reflecting the key principle of circadian rhythms that optimizing daytime activities is crucial for improving nighttime sleep. The application is compatible with both the Android OS and iOS platforms.

Participants are provided with a wrist-worn wearable device (Fitbit Inspire 3, Fitbit Inc., USA) and are instructed to wear it throughout the 4-week study period, except for charging or if it causes significant discomfort. This integrated platform, consisting of a Fitbit device and a SOMDAY application, enables both passive and active data collection. The digital data to be collected for this study is categorized into four main domains: (1) sleep metrics, (2) activity data, (3) heart rate data, and (4) application-derived data.

The first three domains of data, which include sleep metrics, activity data, and heart rate data, are obtained passively from wearable devices and constitute the passive digital phenotyping component. The fourth domain, application data, is collected using a smartphone application and will represent the active digital phenotyping component. These data are processed to derive a comprehensive set of digital phenotypes for subsequent analyses.

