#### Data processing and feature generation

2.5.3

The raw digital data from the wearable devices and the SOMDAY smartphone application undergo a rigorous processing pipeline to generate a comprehensive set of digital phenotypes. This approach is not limited to a single analytical plan, and the processed data can be used for various advanced statistical and computational analyses, such as machine learning, to explore the complex relationships between different data modalities and identify meaningful patterns. The processing strategies for each data modality are meticulously designed to provide a rich dataset for subsequent analyses aimed at elucidating biopsychosocial phenotypes of sleep.

The periodic nature of sleep and activity is the key focus of our analysis. Raw data from wearable devices, including continuous heart rate and step counts, will be processed to extract a range of clinically relevant features. For continuous variables such as heart rate and step counts, cosinor analysis (58, 59) will be performed to characterize circadian rhythms. This will involve processing the data within 72-hour intervals to derive key circadian rhythm parameters, including midline estimating statistic of rhythm (MESOR), amplitude, and acrophase. MESOR represents the rhythm-adjusted mean and provides a robust measure of the average parameter level over time. Amplitude quantifies the extent of predictable variation within the circadian cycle, reflecting the strength of the rhythm. The acrophase indicates the timing of the peak value, which offers insight into circadian alignment or misalignment.

In addition, a range of other activity-related metrics will be calculated to provide a more detailed view of daily patterns. These will include the least active 5-hour period (L5), the most active 10-hour period (M10), interdaily stability (IS), and intradaily variability (IV) (60). L5 and M10 will be calculated using the moving average method to identify minimum and maximum activity periods, respectively. IS quantifies the day-to-day regularity of a rhythm, whereas IV measures rhythm fragmentation within a day. These features will be segregated by weekdays and weekends to capture distinct lifestyle patterns.

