#### Data adherence and privacy

2.5.4

The integration of the SOMDAY application with the Fitbit platform enables automatic synchronization of both active and passive data, allowing the research team to monitor participant compliance in real time. This system also allows participants to view their daily summaries, such as sleep and activity data, directly within the SOMDAY interface, thereby increasing self-awareness and motivation to adhere to the study protocol. In addition, an automated notification system sends encouragement messages when adherence for either data type falls below 50% within a given week, which further helps reduce participant fatigue and dropout. To ensure data security, all information collected through the SOMDAY application and Fitbit platform was encrypted during transmission and stored on an independent, access-restricted server maintained by the research team. Database encryption key management was implemented to prevent key leakage and unauthorized access. User access rights and activity logs were continuously monitored, and sensitive data were encrypted to prevent the exposure of personal identifiers.

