#### Unsupervised learning for phenotype discovery

2.8.4

*Clustering analysis*: Data-driven identification of insomnia subtypes will utilize multiple clustering algorithms, including k-means, hierarchical clustering, and Gaussian mixture models. Clustering will be performed using standardized digital phenotyping features, and the optimal cluster number to be determined using silhouette analysis, gap statistics, and clinical interpretability.

*Dimensionality reduction*: Principal component analysis (PCA) and t-distributed stochastic neighbor embedding (t-SNE) will reduce data dimensionality while preserving important patterns. Uniform manifold approximation and projection (UMAP) will provide an additional visualization of high-dimensional relationships.

*Cluster validation*: Discovered clusters will be validated using internal measures (silhouette width and Dunn index) and external validation through clinical outcomes and biomarker profiles. Stability analysis using bootstrap resampling will assess cluster robustness across different sample compositions.

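### Interdaily stability is computed on unequal numbers of usable days, so participants with less wear look more regular in the group comparison and the clustering

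*Protocol article*

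**What the plan says.** Participants wear a wrist device for four weeks and are "instructed to wear it throughout the 4-week study period, except for charging or if it causes significant discomfort" (section 2.5, Digital phenotyping). If weekly adherence drops, the system "sends encouragement messages when adherence for either data type falls below 50% within a given week" (section 2.5.4). This is a prompt to the participant, not an analysis rule.

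Section 2.5.3 derives L5, M10, IS and intradaily variability (IV) from activity data. On the last two: "IS quantifies the day-to-day regularity of a rhythm, whereas IV measures rhythm fragmentation within a day". It adds: "These features will be segregated by weekdays and weekends to capture distinct lifestyle patterns". A fixed window is given only for the cosinor parameters: "This will involve processing the data within 72-hour intervals to derive key circadian rhythm parameters". No window or number of days is given for IS.

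For device non-wear, section 2.8.1 states that "short-term gaps will be interpolated using Kalman smoothing to preserve temporal continuity", "whereas longer missing periods will be excluded from time-series analyses". It also promises sensitivity analyses on missing-data assumptions in general terms. Section 2.8.2 compares the cohorts, with ANCOVA for confounders such as age, sex and comorbidity. Section 2.8.4 looks for insomnia subtypes: "Clustering will be performed using standardized digital phenotyping features".

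**The concern.** IS is the variance of a person's average 24-hour profile divided by the total variance of that person's data. An average over few days still carries much of the day-to-day noise, and that noise counts as profile variance. The estimate therefore rises as the number of days falls, even when behaviour is identical.

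Followed as written, the plan leaves participants with different numbers of usable days and then puts their IS values on one scale. If wear differs between cohorts, part of an IS difference is a wear difference. If wear differs within the insomnia group, the clustering may pick up wear and report it as a regularity phenotype. Group differences and data-driven subtypes are two of the three primary objectives in section 2.8.

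The bias does not need informative missingness. It arises even when days are lost completely at random.

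**Working it through.** **The plan's own figures.** The article gives no figure for IS, usable days or attrition, so there is none to reproduce on this point. The design figure in section 2.9 (about 80% power for d ≈ 0.36 with 240 and 80 participants) reproduces at 79.6% and is not affected.

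**Inputs.**
- Monitoring: 4 weeks = 28 days (section 2.5). With the weekday/weekend split: 28 × 5/7 = 20 weekdays and 28 × 2/7 = 8 weekend days at most.
- True (long-run) IS: not in the article. Assumed IS₀ = 0.40, range 0.2 to 0.6.
- Between-person SD of true IS: not in the article. Assumed 0.05 to 0.10.
- Share of participants who stop early: not in the article. Assumed 10% to 30%.

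**Formula.** With profile variance P and noise variance E, IS₀ = P/(P + E). Over D days the variance of the mean profile is about P + E/D, so the expected estimate is about

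IS₀ + (1 − IS₀)/D.

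At D = 1 the mean profile is the data, and IS = 1 by construction.

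**Results for IS₀ = 0.40** (simulation: 24 hourly bins, 600 replicates, independent noise):

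| Days | Formula | Simulated mean |
|---|---|---|
| 28 (all days, full wear) | 0.421 | 0.419 |
| 14 (all days) | 0.443 | 0.440 |
| 20 (weekdays, full wear) | 0.430 | 0.431 |
| 5 (weekdays, one week) | 0.520 | 0.516 |
| 8 (weekend days, full wear) | 0.475 | 0.475 |
| 2 (weekend days, one week) | 0.700 | 0.691 |

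The rise also appears with autocorrelated noise (AR(1), 0.5): weekend IS 0.459 on 8 days and 0.671 on 2.

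**Shifts relative to full wear**, (1 − IS₀)(1/D − 1/D_full), with the range for IS₀ from 0.6 to 0.2:
- All days, 14 against 28: 0.60 × 0.0357 = 0.021 (0.014 to 0.029).
- Weekdays, 5 against 20: 0.60 × 0.15 = 0.09 (0.06 to 0.12).
- Weekend, 2 against 8: 0.60 × 0.375 = 0.225 (0.15 to 0.30).

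**In standardised units** (simulated, with the assumed between-person SD of 0.05 to 0.10):
- Stopping at 7 days: 0.6–1.1 on all days, 0.8–1.4 on weekdays, 2.2–3.1 on weekends.
- Stopping at 14 days: 0.2–0.5, 0.3–0.6 and 0.7–1.1.

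**Effect on the cohort comparison.** Suppose, as an illustration, that one cohort had 10 percentage points more one-week records than the other. Its mean weekend IS would rise by roughly 0.10 × 2.2 to 0.10 × 3.1, or about 0.2 to 0.3 SD. On weekdays the rise would be 0.10 × 0.8 to 0.10 × 1.4, or about 0.1 SD.

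**Effect on clustering.** Two-cluster k-means on 249 simulated participants with no true subtypes, early stoppers at 7 days. Share falling in the high-IS cluster:
- Weekday and weekend IS only: 87–97% of stoppers, 11–46% of completers.
- With 8 independent other features added: 87–94% against 14–44%.
- With 8 strongly inter-correlated other features that dominate the split: 53–56% against 47–51%, so the artefact nearly vanishes.

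**Equal days.** With IS computed on the same number of days for everyone (SD 0.10, 20% stoppers, at 14, 7 or 4 days), the stopper-completer difference falls to between 0.00 and 0.17 SD. The high-IS cluster then holds 52–57% of stoppers and 50–56% of the others.

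**The case against.** The article nowhere says that IS is computed on whatever days are left. The exclusion sentence refers to time-series analyses, a label that section 2.8.3 uses for mixed models of daily data. Valid-day definitions and a minimum wear time commonly sit in an analysis plan or full protocol, and neither is shown. IS is one of many digital features. Clusters are also to be checked against clinical outcomes and biomarkers, and sensitivity analyses on missing data are promised.

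Part of this stands. The absence of a minimum-wear rule is not itself a finding, and the link from the exclusion rule to IS is a plain reading, not a literal statement. The size depends on wear data that the article does not give.

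The core remains. Unworn days yield no data unless filled in, and filling in is reserved for short gaps, so day counts will differ whatever the label means. A minimum-wear rule would limit the bias but not remove it while counts above the minimum still vary. The stated safeguards do not target it:
- Standardising across participants leaves each person's dependence on D intact.
- False-discovery-rate correction does not address bias.
- Bootstrap stability can confirm a reproducible artefact.
- Sensitivity analyses on missing-data assumptions miss a bias that exists under random loss.
- Validation against clinical outcomes can be passed by a wear-defined cluster if wear relates to severity.

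Three stronger readings are tempting but unsupported. A reader might infer that people who withdraw after a few days are kept and will form their own cluster, but the article does not describe how withdrawals are handled. A reader might take the adherence message in section 2.5.4 as an expectation of low wear, but it only says what happens if wear drops. And a reader might divide the shift by the sampling SD of a single estimate, for example (0.516 − 0.419)/0.027 = 3.6 for 5 days against 28. Comparison and clustering depend on the between-person spread, so that yardstick exaggerates.

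**Conclusion.** The point holds as a bias in one feature, with a known direction and a known form. IS is inflated by about (1 − IS)/D, and the plan compares and clusters it across unequal D. The weekday/weekend split makes it worse because it shortens every record, most of all the weekend one.

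The size is modest for long records: about 0.02 on all-days IS when 14 of 28 days remain. It is large for short ones: about 0.09 on weekday IS and about 0.22 on weekend IS when one week remains, at an assumed true IS of 0.40. Whether this matters in practice depends on how many participants have short records and on the between-person SD of IS, neither of which the article gives. A low-wear cluster is possible. How likely it is depends on the weight of IS among the clustering features. The bias should be removed before the features are computed, but it does not undermine the study as a whole.

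**What to change.** Compute IS for every participant on the same number of valid, clock-aligned days, set separately for weekdays and weekends. One option is to average IS over blocks of 5 valid weekdays and over blocks of 4 valid weekend days. Full wear then gives 20/5 = 4 weekday blocks and 8/4 = 2 weekend blocks. Each block is still inflated (to about 0.52 and 0.55 for a true IS of 0.40), but in the same way for everyone. A common block of 7 calendar days would not do, because it holds only about 2 weekend days.

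Alternatively, apply the finite-day correction (IS − 1/D)/(1 − 1/D). On the simulated means it returns (0.475 − 0.125)/0.875 = 0.40 for 8 weekend days and (0.691 − 0.5)/0.5 = 0.38 for 2. With the autocorrelated noise it over-corrects a 2-day record to (0.671 − 0.5)/0.5 = 0.34, so a minimum is still needed. Either way, set IS to missing below that minimum.

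Report usable days by cohort and by cluster, and check that usable days do not predict cluster membership before calling a cluster a subtype.

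The cost is recoding one feature and adding one table and one check. Collection is complete and the analyses are still described as future, so no new data are needed. The downside is that participants with few days lose the IS feature and must be left out of any clustering that uses it. IS, especially weekend IS, is also less precise. Block values are not comparable with IS computed on full records elsewhere.
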